##### Resting-state functional connectivity

Resting-state functional MRI data will be acquired using simultaneous multislice echo planar imaging sequence (Miller et al., 2015) with a scan time of ~5 mins, with the following parameters: TE/TR = 30 ms/1,000 ms, 300 frames, slice thickness = 2.5 mm, and 2.5 mm isotropic in-plane resolution, and slice acceleration factor (SMS) of 4. A matching B0 field map will be acquired with an approximate scan time of 1.5 min, with the following parameters: TE 1 = 4.92 ms, TE 2 = 7.38 ms, TR = 688 ms.

#### Exploratory outcomes

We will collect the following exploratory outcomes at baseline, 8-week, and 26-weeks: quality of Life [EQ-5D; (Herdman et al., 2011)], anxiety [GAD-7; (Spitzer et al., 2006)], mindfulness [FFMQ-SF; (Baer et al., 2006)], global cognition [MoCA; (Nasreddine et al., 2005)], general vascular burden [CIRS-G vascular subscale; (Linn et al., 1968)], and brain iron accumulation/microbleeds *via* quantitative susceptibility mapping. A detailed description of exploratory outcomes can be found in Table 1.

**Table 1 T1:** Exploratory outcome measures for all participants, administered at 0 weeks (baseline), 8 weeks (end of intervention) and 26 weeks (follow-up).

**Exploratory outcomes**	**Description**
EuroQol-5D	The EQ-5D is a well-validated quality of life scale used in clinical depression trials. Research has shown that a patient's quality of life influences their level of help-seeking and treatment adherence. As such, it is important to examine patients' assessment of their own wellbeing and functioning.
Generalized anxiety disorder questionnaire (GAD-7)	The GAD-7 is a brief self-report measure of anxiety which is useful to measure in this population given the high comorbidity of depression and anxiety in late life, as well as the associated lower quality of life and poorer treatment response seen with anxiety.
Short-form of the five facet mindfulness questionnaire (FFMQ-SF)	The FFMQ-SF has been found to be a valid and reliable measure of dispositional mindfulness in depressed older adults in assisted care. We chose the short form to reduce participant burden.
The montreal cognitive assessment (MoCA)	The MoCA examines seven different cognitive domains, including visuospatial/executive functioning; naming; attention/concentration; language; abstraction; delayed recall; and orientation in time and place. The MoCA will be used to screen out patients with dementia who may be less likely to benefit from this study (MoCA score <19), and to measure global cognition at baseline, 8-week, and 26-week time points.
Cumulative illness rating scale-geriatric (CIRS-G) vascular subscale	The Cumulative Illness Rating Scale (CIRS-G) is a user-friendly but comprehensive review of common medical problems of the elderly by organ system. The vascular subscale focuses on common vascular issues (e.g., hypertension, atherosclerosis disease, history of aortic aneurysm, etc.). We chose to include the CIGS-R vascular subscale because vascular risk factors can account for mood disorder and functional impairment among geriatric patients.
Quantitative susceptibility mapping (QSM) assessment based on T2^*^-weighted imaging	T2^*^ and magnetic susceptibility mapping uses a multi-echo gradient echo sequence which is differentially sensitive to myelin and iron content, and consequently provides an important marker for iron accumulation and microbleeds in the brain. Acquisition parameters: 12 echoes TE = [2.84, 6.20, 9.56, 12.92, 16.28, 19.64, 23.00, 26.36, 29.72, 33.08, 36.44, 39.80] ms, TR = 44 ms, α = 15°, FOV = 192 x 180 x 144 mm^3^, slice oversampling 11%, 1 mm^3^ isotropic voxels, GRAPPA = 2, 12 min. We will fit a decaying exponential across the echo times to determine the T2^*^ signal at each voxel. This measure is sensitive to vascular pathology that may lead to neurodegeneration. We will use it to detect changes in vascular pathology over the course of the interventions and follow-ups, as well as to assess baseline vascular risk factors that may impact the course of treatment.

### Statistical analyses

Primary analyses will be based on intent-to-treat, not per-protocol. However, we will additionally conduct sensitivity analyses for those participants who completed at least 75% of intervention sessions.

*Analysis 1*. To assess whether MBCT improves symptoms of LLD and quality of life compared to an active control (HEP) over 8 and 26 week samples, we will build generalized mixed models to test the following hypotheses: *1A*. The MBCT group will have a greater reduction in Hamilton Depression Scale (HAM-D17) scores compared to HEP controls, and *1B*. The MBCT group will maintain these improvements at 26-weeks.

*Analysis 2*. Investigate the impact of MBCT on cognitive deficits in LLD we will analyze the Z-scores at initial, 8-week and 26-week follow-up of MBCT and HEP groups using generalized mixed models to test the following: *2A*. Compared to HEP, MBCT will be associated with greater improvements in executive functioning and processing speed scores, and *2B*. The MBCT group will maintain these improvements at 26-weeks.

*Analysis 3:* The neuroimaging analysis is a pilot that will generate effect size estimates for future definitive studies examining neural mechanisms of MBCT in LLD, including the following: *3A*. MBCT patients will be superior to HEP controls with respect to increases in hippocampal volume, increases in default network resting-state functional connectivity, and decreases in executive network resting-state functional connectivity at 8 weeks, and *3B*. The MBCT group will maintain these changes at 26-weeks.

To assess changes in hippocampal volume and functional connectivity, we will implement whole-brain spreading models as in our previous work (Lifshitz et al., 2019), to specifically test for voxels in which the MBCT group exhibits change from baseline to 8 and 26-weeks while the control group does not. To assess functional connectivity, we will implement a standard seed-based analysis using 10 mm seeds positioned in the dorsolateral prefrontal cortex and posterior cingulate cortex, indexing connectivity of the executive network and default network, respectively. Vertex-wise analyses will be performed using the RMINC toolbox (Lerch et al., 2017), as in previous work (Lifshitz et al., 2019). Analyses will consider age, sex, and brain volume/connectivity; clinical/cognitive variables will be considered as independent variables. We will use False Discovery Rate to correct for multiple comparisons (Genovese et al., 2002).

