## Methods

### Study design

A multi-site phase III RCT with 213 LLD patients, randomized 1:1 to MBCT or HEP. This will be an 8-week two-arm, assessor-blind RCT of MBCT vs. HEP in LLD, at various centers in Montreal. Participants will attend three assessment sessions (baseline/0 weeks, 8 weeks, and 26 weeks) in a research-hospital setting. Participants will attend either MBCT or HEP during group sessions for 2 h/week, for 8 weeks. We will assess change in:

Depression scores (HAM-D17) in the MBCT arm compared to HEP at 8 weeks. We will also assess whether participants in the MBCT arm will continue to have reduced depression scores at the 26-week follow-up (Primary outcome).Executive functioning and processing speed in the MBCT arm compared to HEP at 8 weeks. We will also assess whether participants in the MBCT arm will continue to have improved cognitive scores at the 26-week follow-up (Secondary outcome A).Hippocampal volume, default network resting-state functional connectivity and executive network resting-state functional connectivity at 8 weeks. We will also assess whether participants in the MBCT arm will maintain greater increases in hippocampal volume, increases in default network resting-state functional connectivity, and decreases in executive network resting-state functional connectivity at the 26-week follow-up (Secondary outcome B).

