##### Brain biomarkers

Functional and structural magnetic resonance imaging (MRI) will be collected from a subset of the overall sample (*n* = 40) at Montreal sites (McGill and UdeM) at baseline, 8-weeks, and 26-weeks in a 3T Siemens Prisma scanner. All imaging data will be acquired at the Douglas Institute site to avoid known issues of scan-site variability (Hainline et al., 2018). Based on our experience collecting fMRI data with geriatric patients, we have allotted 60 min scan-time for each assessment (including setup).

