#### Power analysis

We estimate a total sample size of 213 participants randomized, with 170 study completers (20% loss to follow-up) based on effect sizes (ES) estimated from our preliminary data and meta-analyses of adult mindfulness-based interventions RCTs. In our preliminary RCT (Torres-Platas et al., 2019), 8-week MBCT was associated with a 7.9 (SD: 4.4) point improvement on PHQ-9 scores vs. TAU 4.0 (SD: 4.7). Cohen's d = (7.9–4.0)/4.55 = 0.86. Two meta-analyses of mindfulness RCTs (*n* = 35 studies (Hofmann et al., 2010) and *n* = 12 studies (Strauss et al., 2014) found ES (Hedge's g) = 0.50 vs. active control, and ES (g) = 0.41–0.64 vs. TAU in adults with depressive symptoms.

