## Discussion

There is an urgent need to test potentially cost-effective, accessible, tolerable, and scalable non-pharmacological treatments for LLD. The proposed study will make use of an active control group, rater-blinding, and validated assessment tools to collect depression and executive function scores and neuroimaging, as well as a number of exploratory outcome measures, which allow us to reliably collect this data with a high degree of fidelity. If MBCT is found to be effective in treating LLD, the collection of neuroimaging data will provide insight on the mechanisms of action of this intervention. MBCT could lower the burden of complications associated with LLD, including disability, increased mortality, suicidality, and risk of cognitive decline (Gildengers et al., 2008; Gilman et al., 2017). In a meta-analysis of younger adult patients, MBCT has been found to be effective in preventing depression relapse (Kuyken et al., 2016), and more recently in treating acute depression and other mental illnesses in real world healthcare settings (Tickell et al., 2020). Since MBCT is delivered in groups and could potentially be adapted into an online intervention, it is scalable in a variety of settings, including primary care. Additionally, future research could examine the cost-effectiveness of MBCT compared to individual psychotherapy or pharmacology for LLD, potentially lowering the direct health-care costs related to LLD (Snow and Abrams, 2016). Elucidating the neural mechanisms of MBCT will pave the road to optimized combination treatment approaches (e.g., with antidepressants or brain stimulation targeting complementary brain circuits). This mechanistic knowledge has the potential to inform patient-tailored precision medicine and target preventative measures for this vulnerable population which has a higher risk for dementia.

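### The 40-person imaging analysis is defined as an effect-size pilot but carries superiority and maintenance statements, an uncaveated secondary rank and a one-arm-changes test; it should estimate the between-arm difference with confidence intervals

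*Protocol article*

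**What the plan says.** The protocol article gives the imaging analysis several statuses.

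- **Purpose** (Statistical analyses, Analysis 3): "The neuroimaging analysis is a pilot that will generate effect size estimates for future definitive studies".
- **Hypotheses** (same sentence): under 3A, "MBCT patients will be superior to HEP controls with respect to increases in hippocampal volume", with matching statements for default and executive network connectivity at 8 weeks. Under 3B, the MBCT group keeps these changes at 26 weeks.
- **Rank** (Study design): the list of imaging measures ends "decreases in executive network resting-state functional connectivity at the 26-week follow-up (Secondary outcome B". It stands beside the cognitive outcomes (Secondary outcome A), with no mention of a pilot. The Outcomes section also describes the measures under Secondary outcomes, although an Exploratory tier exists and already holds another MRI measure (QSM).
- **Size** (Brain biomarkers): MRI data "will be collected from a subset of the overall sample (*n* = 40) at Montreal sites".
- **Method** (imaging paragraph of Statistical analyses): whole-brain models look for voxels where MBCT changes from baseline and the control group does not. Connectivity is seed-based, and multiple comparisons are handled by False Discovery Rate.
- **Claim** (Discussion): if MBCT proves effective, "the collection of neuroimaging data will provide insight on the mechanisms of action of this intervention".

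The Power analysis section gives no effect size, power or precision for imaging.

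**The concern.** A pilot meant to supply effect sizes should report a between-arm difference and its uncertainty. Superiority and maintenance are conclusions, and a voxel test for change in one arm but not the other is not an estimate of the difference between arms. A reader of the trial report could not tell which status applies.

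Two consequences follow. First, if 3A and 3B are answered as hypotheses, a non-significant result may be taken as absence of effect and a significant one as support for a mechanism. The sample supports neither inference for small or moderate effects. Second, if only voxels passing a threshold are reported, the effect sizes passed to later studies will tend to be too large, which defeats the stated purpose.

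**Working it through.** **Inputs**

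- Imaging subset: 40 (Brain biomarkers).
- Allocation: "randomized 1:1 to MBCT or HEP" (Study design).
- Loss: the main trial is planned "with 170 study completers (20% loss to follow-up" (Power analysis).
- Benchmark effect: 0.50 against active control (Power analysis). This is a depression-symptom effect. The article gives none for imaging, so it serves only as a yardstick.
- Alpha: not stated. Two-sided 0.05 is assumed, with 0.05/3 shown as a range for three measures.

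**Step 1. The plan's own figure.** 170 / (1 − 0.20) = 212.5, rounded up to 213. This reproduces the stated total. No corresponding figure exists for the 40.

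**Step 2. Patients per arm.** 40 / 2 = 20. With 20% loss, 40 × 0.80 = 32, and 32 / 2 = 16. The range is 16 to 20. It is derived, not stated: randomization is stratified by sex and site, not by imaging participation, so an even split is not assured.

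**Step 3. Power of one simple comparison.** Two-sample t-test with 2n − 2 degrees of freedom and noncentrality d × √(n/2). At d = 0.50 the noncentrality is 0.50 × √10 = 1.58 for n = 20 and 0.50 × √8 = 1.41 for n = 16.

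| | 20 per arm | 16 per arm |
|---|---|---|
| Power at d = 0.50 | 34% | 28% |
| Detectable d at 80% power, alpha 0.05 | 0.91 | 1.02 |
| Detectable d at 80% power, alpha 0.05/3 | 1.06 | 1.20 |

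**Step 4. Precision.** The approximate 95% CI half-width of a standardised difference is 1.96 × √(2/n + d²/(4n)). At d = 0.50:

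- n = 20: 1.96 × √(0.1000 + 0.0031) = 0.63, interval −0.13 to 1.13.
- n = 16: 1.96 × √(0.1250 + 0.0039) = 0.70, interval −0.20 to 1.20.

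Both intervals include zero and values above 1 SD.

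**Step 5. The one-arm-changes test.** The wording may describe a proper interaction model. If instead it means significant in MBCT and not significant in HEP, a single test can be checked as follows. Assume the same true within-arm change in both arms, 0.3 to 0.5 SD, and independent arms. Let p be the one-sample t power at two-sided 5%. The chance that MBCT is significant and HEP is not is p(1 − p).

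- n = 16: p = 0.20 gives 0.16; p = 0.47 gives 0.25.
- n = 20: p = 0.25 gives 0.19; p = 0.57 gives 0.25.

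On that reading, an apparent MBCT-specific change arises 16 to 25% of the time at a single location, before FDR correction, with no difference between arms.

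**The case against.** The case on the other side is substantial.

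- **The limitation is disclosed.** The article says pilot, states n = 40 and claims no imaging power. It is tempting to infer a failed sample-size calculation, but there is none to fail. This stands.
- **The framing differs from Analyses 1 and 2.** Those are introduced as tests; Analysis 3 is introduced as generating estimates, so 3A and 3B could be read as naming contrasts to estimate. This is weakened by the next paragraph, which plans FDR-corrected voxel tests.
- **Secondary does not mean confirmatory.** A secondary outcome need not be powered. This stands. The fault is the missing caveat and the superiority wording, not the rank alone.
- **No joint criterion.** A reader might infer that all three measures in 3A must succeed together. The article sets no such rule, so no joint power figure applies.
- **Clinical variables are included.** A reader might infer that brain and clinical measures are never linked. The imaging paragraph brings clinical and cognitive variables into the models, and the subgroup section relates baseline neuroimaging to treatment response. Further model detail may sit in the full plan.
- **The mechanism sentence is conditional.** It applies only if MBCT works, and it speaks of insight, not proof. This stands, but it carries no pilot caveat.
- **The yardstick is imperfect.** The 0.50 is a depression effect, and a simple t-test is not the planned covariate-adjusted voxel analysis. This stands, so the power figures are indicative only.

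**Conclusion.** The point holds as an inconsistency of status and a mismatch between purpose and method. The declared pilot carries superiority and maintenance statements, a secondary rank without qualification, and a test that does not deliver the effect sizes it exists to provide.

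Size: on the range above, the subset can reliably detect only a difference of roughly 0.9 to 1.0 SD on one unadjusted measure, and its estimates will be wide. It can neither confirm nor exclude small-to-moderate effects. This rests on three assumptions: 1:1 allocation and 20% loss carry over to the subset, alpha is two-sided 5%, and a simple two-group comparison is an adequate guide.

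A reader might go further and say the imaging can show nothing. The documents do not support that: a very large effect on a single measure could be detected, and estimation is a legitimate aim at this size. The primary outcome and the main-trial sample size are untouched. Severity is minor; this is a cheap improvement.

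**What to change.** 1. **Study design:** mark Secondary outcome B as a pilot outcome, or move it to the exploratory tier.
2. **Statistical analyses:** replace 3A, 3B and the one-arm-changes test with text such as: *For each prespecified imaging measure, the MBCT-minus-HEP difference in change from baseline will be estimated at 8 and 26 weeks with a 95% confidence interval and reported whatever its significance. No conclusion of superiority, maintenance or absence of effect will be drawn.*
3. **Discussion:** describe any mechanistic insight as hypothesis-generating.

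The changes need no additional patients or scans, and the estimates use data already planned. The price is a more modest imaging claim, which matches the purpose the article already states.

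### The stated imaging test, change in MBCT with none in HEP, is not the between-arm difference in change that hypothesis 3A asserts

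*Protocol article*

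**What the plan says.** All references are to the Protocol article.

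- **Hypothesis.** Under Statistical analyses, Analysis 3, hypothesis 3A is a comparison of arms: "MBCT patients will be superior to HEP controls with respect to increases in hippocampal volume". It continues with increases in default network connectivity and decreases in executive network connectivity at 8 weeks. Hypothesis 3B concerns the MBCT arm alone: "The MBCT group will maintain these changes at 26-weeks".
- **Test.** The next paragraph of the same section says that whole-brain spreading models, taken from the group's cited earlier work, will be used "to specifically test for voxels in which the MBCT group exhibits change from baseline to 8 and 26-weeks while the control group does not".
- **Multiplicity.** "We will use False Discovery Rate to correct for multiple comparisons". No level is given.
- **Status.** "The neuroimaging analysis is a pilot that will generate effect size estimates for future definitive studies". Study design lists the imaging measures as Secondary outcome B.
- **Size.** Under Brain biomarkers, MRI "will be collected from a subset of the overall sample", with n = 40.

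No arm-by-time term or other between-arm contrast of change is named for imaging. The treatment interactions that the article does name, under Subgroup analyses, are with site and with group size.

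**The concern.** The hypothesis and the test describe different quantities. Hypothesis 3A is about the size of the change in MBCT minus the change in HEP. The stated test looks for a conjunction: change in one arm and none in the other.

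The conjunction fails as a test of 3A in two ways. First, its second half cannot be established by a non-significant result in a small arm, so a location where both arms change equally can show the pattern by chance. HEP is an active control with gentle exercise and home practice matched to MBCT, so change in both arms cannot be ruled out. Second, a location where both arms change, but MBCT changes more, supports 3A and yet does not fit the pattern.

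At stake is the mechanistic reading of the trial. A brain change could be credited to MBCT when the two arms did not differ, or a real difference could be passed over.

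**Working it through.** The article gives no power, alpha or error rate for imaging, so there is no figure of its own to reproduce. The calculation below shows what the stated pattern would do **if** it were sought with one test in each arm.

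**Inputs**

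- Scanned participants: 40 (Brain biomarkers).
- Allocation: "randomized 1:1 to MBCT or HEP" (Study design). I assume that this holds in the subset, which gives 40 / 2 = 20 per arm.
- Attrition: "with 170 study completers (20% loss to follow-up") (Power analysis). I assume the same rate for scans: 20 × 0.8 = 16 per arm.
- True within-arm change, equal in both arms: 0.3, 0.5 and 0.7 SD of the change score. These values are assumed; the article gives none.
- Per-location threshold: two-sided 0.05 uncorrected, and 0.001 as an assumed stand-in for a corrected threshold.

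**Formula**

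Let p be the power of a one-sample t-test of change in one arm (noncentral t, n − 1 degrees of freedom, noncentrality d√n). With independent arms and equal true change, the probability that MBCT is significant and HEP is not is p(1 − p).

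**Example** (16 per arm, d = 0.5, threshold 0.05): the noncentrality is 0.5 × √16 = 2.0, so p = 0.465 and p(1 − p) = 0.465 × 0.535 = 0.249.

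**Results with equal true change in both arms**

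| Per arm | Threshold | 0.3 SD | 0.5 SD | 0.7 SD | Between-arm test, MBCT direction |
|---|---|---|---|---|---|
| 16 | 0.05 | 16.2% | 24.9% | 19.0% | 2.5% |
| 20 | 0.05 | 18.6% | 24.6% | 13.2% | 2.5% |
| 16 | 0.001 | 1.1% | 4.9% | 13.8% | 0.05% |
| 20 | 0.001 | 1.6% | 8.0% | 20.0% | 0.05% |

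With no change in either arm there is no inflation: 0.05 × 0.95 = 4.75% over both directions. The fault appears once both arms change.

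**Simulation check** (100,000 trials, 20 per arm, 0.5 SD in both arms, threshold 0.05): the pattern appeared in 24.5% of trials, and the two-sample test of change rejected in 5.1% (two-sided). Only about 10% of the trials that showed the pattern also had a between-arm p below 0.05.

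**Missed differences.** Take 20 per arm, a threshold of 0.05, a HEP change of 0.5 SD and a true difference of 0.8 SD. The pattern appears with probability 0.9998 × (1 − 0.5645) = 43.5%, while the between-arm test has 69.3% power. With 16 per arm the figures are 53.4% and 59.1%. This loss depends on the HEP change. With no HEP change and 20 per arm, the pattern appears more often than the between-arm test rejects (87.8% against 69.3%). So its frequency depends on the HEP change as well as on the difference between arms.

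**The case against.** **The article does not say that two within-arm tests will be run.** It names a spreading model defined in a cited source that is not at hand, and a single joint contrast is possible. This stands as a limit on the percentages. It does not remove the mismatch: the stated target is still change in one arm with none in the other, and a contrast built on it would not be the plain difference in change.

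**The largest percentages ignore the planned False Discovery Rate correction.** This also stands. At an assumed per-location threshold of 0.001 the figures fall to about 1% / 5% / 14% with 16 per arm, and at 0.0001 to about 0.2% / 1.0% / 4.0%. They remain well above the nominal rate, because the correction works across locations and does not alter which contrast is tested.

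**A reader might infer that the pilot effect sizes will be inflated because they come from selected voxels.** The article does not support that. Under Hippocampal volume it plans MAGeT volumetry, which gives a volume for each participant without voxel thresholding. The connectivity seeds are fixed in advance. Nothing says that estimates will be taken from thresholded voxels.

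**A reader might also point to the imprecision of a pilot of this size.** With 16 per arm, the 95% half-width on a between-arm standardized difference is about 1.96 × √(2/16) = 0.69. That follows from the sample size and would be the same under the correct contrast, so it is no evidence of this fault.

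**The imaging is a pilot in 40 of 213 participants, and no success rule is attached to Secondary outcome B.** This is fair and lowers the severity.

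**Conclusion.** The point holds as a mismatch between hypothesis 3A and the stated imaging test. As written, the test does not target the between-arm difference in change, and no other part of the article names that contrast for imaging.

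The size of the error is conditional. With equal true change of 0.3 to 0.7 SD, 16 per arm and two separate within-arm tests, the pattern arises at a single location in about 16% to 25% of trials at an uncorrected 0.05, and in about 1% to 14% at an assumed 0.001. The numbers per arm, the changes, the thresholds and the two-test reading are all assumptions, so these figures illustrate the fault and do not forecast the planned analysis.

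Severity is moderate. Only the pilot imaging outcome is affected. The HAM-D17 and cognitive analyses use mixed models with between-arm hypotheses and are untouched.

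**What to change.** In the imaging paragraph of Statistical analyses, replace the stated target with the MBCT-minus-HEP difference in change from baseline (the arm-by-time contrast), tested at 8 weeks and separately at 26 weeks, with the False Discovery Rate correction kept for the maps.

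For the pilot aim, report the measures already planned as between-arm differences with 95% confidence intervals: MAGeT hippocampal volume, connectivity from the posterior cingulate seed, and connectivity from the dorsolateral prefrontal seed.

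If the spreading model already fits this contrast, one sentence saying so would settle the point. The cost is wording only, with the same scans and no new data. The change should be made before the imaging results are analysed.

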#### Health-enhancement program

HEP teaches health-enhancing techniques and was designed by University of Wisconsin and NIH as a manualized active control group program for mindfulness-based intervention trials (Sullivan et al., 2011; MacCoon et al., 2012). We have tailored HEP to be structurally equivalent to MBCT, with similar-sized groups, meeting weekly for 2 h for 8 weeks, and similar amount of home practice (~30 min/day, 6 days/week). HEP controls for several non-specific factors in mindfulness groups, including: group support/morale, behavioral activation, stigma reduction, facilitator attention, treatment duration, and time spent on home practice. Participants will learn about health promotion, healthy diet, music, and gentle exercise, but not about breathing techniques or meditation.

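### The imaging test looks for change in MBCT that is absent in HEP, which is not the between-arm superiority that hypothesis 3A states

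*Protocol article*

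**What the plan says.** In the protocol article, under Statistical analyses, Analysis 3 sets a between-arm hypothesis for 8 weeks (3A): "MBCT patients will be superior to HEP controls with respect to increases in hippocampal volume", with matching statements for default-network and executive-network connectivity. Hypothesis 3B concerns maintenance at 26 weeks. The same section says what the imaging is for: "The neuroimaging analysis is a pilot that will generate effect size estimates for future definitive studies".

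The paragraph that follows describes the method. It says "we will implement whole-brain spreading models as in our previous work", and gives the aim of those models as "to specifically test for voxels in which the MBCT group exhibits change from baseline to 8 and 26-weeks while the control group does not". The contrast weights are not written out, and no group-by-time term or between-arm difference in change is named for imaging. False Discovery Rate is the stated correction for multiple comparisons.

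Imaging is secondary outcome B (Study design) and is collected in 40 participants (Brain biomarkers). On the comparator, the Health-enhancement program section says: "Participants will learn about health promotion, healthy diet, music, and gentle exercise".

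**The concern.** Superiority means that the change under MBCT minus the change under HEP is above zero. The stated target is a pattern: change in MBCT, no change in HEP. The two come apart in both directions.

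- If both arms change equally, there is no MBCT effect relative to HEP. Yet MBCT may reach significance while HEP falls short by chance, which turns a difference in significance into a claimed difference between arms.
- If both arms change clearly and MBCT changes more, MBCT is superior, but the voxel lies outside the target because HEP changed.

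HEP is an active programme with exercise and home practice matched to MBCT, so some change under HEP cannot be ruled out. Practice, ageing and scanner drift would also act on both arms. At stake is the answer to 3A and the usefulness of the pilot: voxels chosen by this rule may show change common to both arms, and a later trial could be planned on them.

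**Working it through.** **Inputs.** From the protocol article: 40 imaging participants and 1:1 randomization, so about 40/2 = 20 per arm. With the article's 20% loss this becomes 20 × 0.8 = 16. The article gives no power or error figure for imaging, so there is none to reproduce. Assumed: an even split of the imaging subset, a per-voxel two-sided alpha of 0.05 before FDR, normal change scores, and true change expressed in SDs of the change score. The article gives no imaging effect size, so a range is shown.

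**Reading 1: two within-arm tests.** The arms are independent, so

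P(rule fires, MBCT up) = P(MBCT significantly up) × [1 − P(HEP significant)],

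where each term comes from a one-sample t test (noncentral t, n − 1 degrees of freedom, noncentrality = change × √n). The comparator is a two-sample t test on change scores.

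*Equal true change in both arms, 20 per arm:*

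| Common change | P(MBCT up) | P(HEP significant) | Rule fires | Between-arm test, same direction |
|---|---|---|---|---|
| 0 | 0.025 | 0.050 | 0.025 × 0.950 = 2.4% | 2.5% |
| 0.3 SD | 0.247 | 0.247 | 18.6% | 2.5% |
| 0.5 SD | 0.565 | 0.565 | 0.565 × 0.435 = 24.6% | 2.5% |
| 0.7 SD | 0.844 | 0.844 | 0.844 × 0.156 = 13.2% | 2.5% |

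With 16 per arm the rule gives 16.1%, 24.9% and 19.0% at 0.3, 0.5 and 0.7 SD. When both probabilities equal p, the product is p(1 − p), which cannot exceed 25%.

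*True superiority with some HEP change, 20 per arm:*

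| MBCT / HEP change (SD) | Rule | Between-arm test |
|---|---|---|
| 0.8 / 0.3 | 70% | 34% |
| 1.0 / 0.3 | 74% | 58% |
| 1.0 / 0.5 | 43% | 34% |
| 1.2 / 0.5 | 43% | 58% |
| 1.5 / 0.7 | 16% | 69% |
| 1.8 / 1.0 | 1% | 69% |

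Once MBCT is almost certain to be significant, the rule's detection is capped at 1 − P(HEP significant). It therefore falls as HEP's change grows, however large the MBCT advantage.

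**Reading 2: one weighted contrast.** Assume, for illustration only, weights −1, +3, −1, −1 on MBCT-pre, MBCT-post, HEP-pre and HEP-post.

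- Expectation with change m in MBCT and h in HEP: 3m − h. With equal change d this is 2d, not 0.
- Variance with unit SD and pre-post correlation ρ: [(10 − 6ρ) + (2 + 2ρ)]/n = (12 − 4ρ)/n.
- A common change of 0.5 SD of the change score is d = 0.5 × √(2(1 − ρ)).

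At ρ = 0.5 and n = 20: d = 0.5, expectation 1.0, standard error √(10/20) = 0.707, z = 1.41, rejection 29%. At ρ = 0.7 and 0.9 the same steps give 21% and 11%. The nominal two-sided rate is 5%. For MBCT 1.5 / HEP 0.7 SD, this contrast rejects in about 100%, 99% and 75% of trials at ρ = 0.5, 0.7 and 0.9, so superiority is not lost there.

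**The case against.** **The contrast is not visible.** The article points to earlier work for the model and gives no weights, and a condensed article commonly leaves exact contrasts to a fuller document. The sentence may be loose prose for an ordinary interaction test. That stands as a limit on Reading 2, where only one weight vector was tried. It does not remove the point: the target itself is printed and differs from 3A. If an interaction test is intended, the sentence misdescribes it.

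**A reader might infer that superiority is missed wherever HEP also changes.** The figures do not support this. With HEP at 0.3 SD, and for MBCT 1.0 / HEP 0.5 SD, the rule detects more than the between-arm test, partly because it is liberal. Under the assumed weighted contrast, the 1.5 / 0.7 SD case is still found in 75% to 100% of trials. The loss is real only under the two-test reading and when HEP's change is clear, and those changes are large and assumed.

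**A reader might also count chance baseline imbalance as a further source of false positives under Reading 2.** A baseline difference b shifts that contrast by 2b, but under randomization its expectation is zero and its spread is already in the variance used above.

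**The inflation needs a common change.** This is correct. With none, the rule holds its level. Nor does the sentence assume that HEP is inert everywhere; it only excludes voxels where HEP changes.

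**Imaging is a pilot.** This limits the consequences. The article also does not say that effect sizes will be computed only in voxels selected this way, so distorted estimates are a risk and not a certainty. But estimates meant for a definitive comparison should come from the between-arm contrast. FDR is no remedy, because it adjusts p-values and leaves the contrast unchanged.

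**Conclusion.** The concern holds in a limited form, with moderate severity. The imaging test as worded does not test hypothesis 3A. Under the two-test reading with 20 per arm, equal change of 0.3 to 0.7 SD in both arms is called MBCT-specific in about 13% to 25% of tests, against 2.5% for the direct comparison. Under the illustrative weighted contrast, false positives are about 11% to 29% at a common change of 0.5 SD, against 5%. Voxels where HEP changes clearly fall outside the worded target (16% versus 69% detection at 1.5 / 0.7 SD under the two-test reading).

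These are per-voxel rates before FDR, and they rest on assumed effect sizes, an even split of the 40 scans and, for the second reading, assumed weights. They show the direction and possible size of the problem and are not predictions for the corrected maps. The documents do not support carrying it over to the trial's main conclusion: the HAM-D17 and cognitive analyses use mixed models for hypotheses that compare MBCT with HEP, and are untouched.

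**What to change.** Replace the sentence that sets the target of the whole-brain models with, for example: *At each voxel or vertex, and for each seed map, hypothesis 3A is tested by the between-arm difference in change from baseline (group-by-time, MBCT minus HEP) at 8 weeks; the same contrast is estimated separately at 26 weeks. Effect sizes are reported for this contrast. Within-arm change maps are descriptive and are not used to infer an MBCT-specific effect.*

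If a fuller analysis document already specifies this contrast, the article's sentence should be aligned with it. The change should be made before the imaging data are analysed. It needs no new scans and uses the same data and software. The price is that fewer voxels may be declared MBCT-specific, and with about 20 per arm the between-arm test has modest power (34% for a difference of 0.5 SD in the cases above).
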